## Abstract

**Background:**

A disturbance in the early colonisation of the gut by microorganisms is associated with an aberrant innate immune system and a variety of clinical conditions later in life. Several factors are considered to influence this initial colonisation, including maternally administered antibiotics during pregnancy and delivery. Recent revisions to international obstetric guidelines have resulted in the exposure of all infants born by caesarean section (CS) to broad-spectrum antibiotics perinatally. To date, the consequences of these new guidelines on neonatal gut colonisation and the associated short- and long-term health implications have not yet been addressed. The aim of this study is to investigate the influence of the timing of antibiotic administration during CS to the mother on the course of neonatal intestinal colonisation up to 2 years of age.

**Methods/design:**

This single-centre randomised controlled trial will recruit 40 women scheduled for an elective CS. The subjects will be randomised to receive 1500 mg of cefuroxime intravenously either prior to the skin incision (*n* = 20) or after clamping of the umbilical cord (*n* = 20). Levels of cefuroxime in cord blood will be determined for exposed neonates. Faecal samples from the children will be collected on days 1, 7 and 28 days and at 2 years old and analysed by 16S sequencing. Shannon-diversity indices, absolute and relative abundances, and unsupervised and supervised classification methods will be used to evaluate the effect of the timing of intrapartum cefuroxime administration on the composition of the microbiota. The outcomes for both study groups will be compared to the intestinal microbiota of vaginally born infants (*n* = 20). To detect possible effects on health state, a questionnaire on health-related issues will be taken at the age of 2 years.

**Discussion:**

In the proposed study, changes in the intestinal microbiota of 40 children born by CS will be followed until the age of 2 years. Research on this topic is necessary since significant effects relating to the timing of antibiotic administration on microbial colonisation may conflict with the current guidelines, as this may have health consequences later in life.

**Trial registration:**

Netherlands Clinical Trial Registry, NTR6000. Retrospectively registered on 25 July 2016.

**Electronic supplementary material:**

The online version of this article (10.1186/s13063-019-3552-8) contains supplementary material, which is available to authorized users.

## Background

The human gut harbours an immense number of microbial cells, estimated to be 10^13^–10^14^ microorganisms [1]. The intestinal microbiota has an essential role in maintaining overall health through several different mechanisms, including protection against pathogens, priming of the immune system, digestion of food and synthesis of essential vitamins [2–4]. In contrast, disturbances of the composition of the intestinal microbiota, especially early in life, are associated with the development of numerous diseases and clinical conditions such as asthma, allergies, inflammatory bowel disease, atopy, necrotising enterocolitis and obesity [2, 5–11]. Despite increasing evidence for this crucial role of the intestinal microbiota in health and disease, little information exists on colonisation early in life and on environmental factors that may affect its composition. Information on microbial dynamics during the neonatal period is pivotal, since early microbial colonisation is considered to be crucial for the microbial composition later in life.

It is generally considered that the foetal gut is sterile and that its colonisation is initiated by exposure to bacteria at birth. However, recent studies have demonstrated that gut colonisation begins in utero [12]. In the first days following birth, environmental factors like (breast)feeding, skin contact and medication further contribute to colonisation [13]. The influence of the route of delivery and the use of antibiotics during a caesarean section (CS) on neonatal microbial colonisation has not been completely clarified. Neonates born by CS have delayed intestinal colonisation compared to vaginally delivered children, since there is no contact with the maternal vaginal and faecal microbiota and the perineal skin [14–16]. In addition, infants born by CS seem to have a decreased microbial diversity, possibly persisting for a prolonged period of at least 2 years [15]. Consequently, these infants are considered to have an increased risk of developing diseases associated with early aberrations in gut microbiota [15, 16]. However, studies on the role of the route of delivery on neonatal colonisation have few participants and short follow-up periods, while the reported results are inconsistent. In addition, there is limited information on the impact of the timing of maternal antibiotic administration during a CS on neonatal colonisation.

According to the guidelines of the National Institute for Health and Care Excellence (NICE) in the United Kingdom [17], prophylactic antibiotics should be given to all women who are undergoing a CS prior to the skin incision. However, the previous guidelines advised administration of antibiotics after clamping of the umbilical cord. This adjusment has been shown to decrease the risk of total infectious morbidities, without an increase in adverse neonatal outcomes. Maternal infectious morbidity affects around 5–10% of women undergoing CS [17, 18]. In a recent meta-analysis, infectious morbidity affected 3.9% of women receiving antibiotics preoperatively, compared to 6.9% of women who received antibiotics after clamping of the umbilical cord (relative risk 0.57). This reduction was predominantly caused by a reduction of endometritis and fewer wound infections [18]. Obviously, when antibiotics are administered prior to skin incision, the infant will be exposed too, whereas infants are not exposed if the antibiotic is administered after clamping of the cord. The effects of this protocol adjustment on neonatal outcomes were exclusively evaluated in the short term, including the effects on suspected sepsis that required a workup [18, 19]. The long-term consequences of the timing and type of antibiotics, such as the influence on neonatal intestinal colonisation, priming of the immune system and on the incidence of auto-immune diseases, like coeliac disease, inflammatory bowel disease, asthma and allergies, have not yet been addressed [20].

## Methods/design

### Study aim

As mentioned previously, infants born by CS have delayed intestinal colonisation and decreased microbial diversity. We hypothesise that exposing these caesarean-delivered infants to intrapartum-administered broad-spectrum antibiotics would further influence the colonisation process. Therefore, the aim of the present study is to evaluate the effects of the timing of the maternal administration of antibiotics during CS on the early neonatal intestinal microbiota and the microbiome until the children are 2 years old.

### Objectives

Thus, the primary objective of this study is to describe the microbiome of the intestinal colonisation in the first month of life and at 2 years of age in two groups of children born by CS: (1) infants exposed to maternally administered antibiotics prior to CS (current NICE guideline) and (2) unexposed neonates from mothers receiving antibiotics after clamping of the cord (former NICE guideline). These outcomes will be compared with each other and to a third study group of vaginally born infants.

Secondary objectives are to investigate whether there are differences at the age of 2 years regarding the health state of children born by CS, in terms of the timing of antibiotic administration. Moreover, we plan to evaluate the association between maternal vaginal and rectal microbiota composition and neonatal gut colonisation in infants born vaginally and by CS. For CS, transmission will be compared between infants born according to antibiotic exposure following the previous and the current guidelines.

### Study design and setting

This is a single-centre randomised-controlled trial. It will be conducted at the Department of Obstetrics and Gynaecology and the Paediatric Department of the Medical Centre of Vrije University (VUmc), which is part of the University Medical Centre Amsterdam. The protocol was designed in accordance with the SPIRIT statement [21] (Additional file 1). The schedule of enrolments, allocation and assessments is given in Fig. 1. A flow diagram of the progress through the planned study phases is shown in Fig. 2.

**Fig. 1 Fig1:**
[figure not shown]
SPIRIT schematic schedule of enrolment, interventions, and assessments. Enrolment of all three groups will be done simultaneously. All assessments will be done the same at the same time point in the study for all three groups, except the umbilical cord blood sample, which will be collected for group A only

**Fig. 2 Fig2:**
[figure not shown]
Flow diagram of study participants

### Patient and public involvement

Patients and the public were not involved in the design of the study.

### Subjects and study population

The study population consists of three groups. The first two groups include 40 pregnant women visiting the outpatient clinic of the Department of Obstetrics and Gynaecology at VUmc during the last trimester of pregnancy. They must have an uncomplicated pregnancy so far and be scheduled for CS. An uncomplicated pregnancy is defined as a normotensive singleton pregnancy, with a normal-weight foetus without maternal or foetal risk factors, delivered without complications at a gestational age of more than 37 weeks. Twenty women will be treated according to the current NICE guidelines for antibiotic administration during CS (group A). These subjects will receive 1500 mg cefuroxime intravenous 30 min prior to skin incision. The remaining 20 women will be treated according to the former protocol (group B) and will be administered 1500 mg cefuroxime intravenous directly after clamping of the umbilical cord. Allocation to a group will be randomised in permuted blocks of 10 using www.random.org. Allocation to a group will be blinded only for the statistician performing the analysis. The third group will include 20 pregnant women with an uncomplicated pregnancy as described above, admitted for outpatient vaginal delivery in VUmc (group C). Exclusion criteria for this group include antibiotics administration during pregnancy or labour and premature rupture of membranes (Table 1). The women delivering vaginally will be recruited at the same time as the women in the other two groups. The neonates born at ≥37 weeks gestational age from mothers included in one of the three study groups will be included following informed consent from both their parents.

**Table 1 Tab1:** Maternal and neonatal exclusion criteria

Maternal exclusion criteria	
Delivery < 37 weeks gestation	
Aged ≤17 years	
Body mass index ≥ 25	
Antibiotic use during pregnancy	
Antibiotic use during labour (group C)	
Immunosuppressive use within 3 months prior to delivery	
Inflammatory bowel disease	
Coeliac disease	
Rupture of membranes before CS (groups A and B)	
Rupture of membranes > 18 h (group C)	
Diabetes mellitus type I or II	
Gestational diabetes requiring insulin	
History of gastro-intestinal surgery	
Alcohol or tobacco use in second or third trimester	
Use of recreational drugs during pregnancy	
Maternal antibiotic use during first month of neonatal life	
Neonatal exclusion criteria	
Congenital gastro-intestinal anomalies	
Gastro-intestinal surgery during first month of life	
Antibiotic or immunosuppressive medication use during first month of life	

Standard demographic and obstetric variables will be collected. Other variables, including nutrition of the neonate (breast milk or formula) during the first month of life, birthweight, Apgar scores after 1 and 5 min and presence of meconium-stained amniotic fluid, will be collected. Data on maternal and neonatal medication use during pregnancy and the first month postnatally will be collected, as well as data on maternal weight, neonatal length and maternal diet (vegetarian or non-vegetarian).

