### Data management and monitoring

All study participants will receive a study identification number. Electronic data will be kept in a secure password-protected database. The data collected will be stored at the research unit in the study centre. All data will be securely stored, backed up and retained for 15 years. Additional consent from both parents will be obtained to store and use this data in future studies. Only relevant members of the research team will have access to the data. A data safety monitoring committee is not required according to the guidelines proposed by Ellenburg et al. [22]*.* The study will be independently monitored at study close-out. No interim analyses will be performed.

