### DNA extraction and microbiota analysis using 16S rRNA gene sequencing

Stool samples from infants will be collected, as reported above, on days 1, 7 and 28 and at 2 years old. DNA will be extracted, as documented previously by Daniels et al. [23]. From the purified faecal DNA, extracts of the V3-V4 hypervariable regions of the bacterial 16S rRNA gene will be amplified, using universal primers S-D-Bact-0341-b-S-17 (forward 5′-CCTACGGGNGGCWGCAG-3′) and S-D-Bact-0785-a-A-21 (reverse 5′-GACTACHVGGGTATCTAATCC-3′) [24]. Sequencing will be performed by LifeSequencing SL (Valencia, Spain) on an Illumina MiSeq instrument (San Diego, California, USA).

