### Statistical analysis

Baseline characteristics will be summarised for all subjects by treatment regimen and compared between groups.

The primary outcome will be differences in the microbiota between the two groups of infants born by CS on day 28. An adaptation of QIIME v1.9.0 [25] will be used to analyse the sequenced data. Briefly, sequences will be clustered into operational taxonomic units based on 97% sequence identity as a proxy for bacterial species using VSEARCH v2.03 against the RDP gold database and by excluding chimeric sequences [26]. Taxonomic assignment will be performed using the RDP classifier [26] against the SILVA119 database [27]. The species diversity (α-diversity) of faecal and salivary samples will be calculated using Faith’s phylogenetic diversity [28] and the Shannon index for diversity [29] and by applying a correction for differences in sequencing depths by rarefaction. Furthermore, absolute and relative abundances as well as unsupervised and supervised classification methods will be used to evaluate the influence of timing of intrapartum cefuroxime administration on the composition of the microbiota.

Clinical outcomes at the 2-year follow-up will be compared using Student’s *t*-test or a Mann–Whitney *U* test for continuous variables depending on whether the variables are distributed normally. A χ^2^ test or Fisher’s exact test will be used to compare normal and non-normal dichotomous variables, respectively. Differences between groups will be presented for continuous outcomes as differences in means or differences in medians (for normal or non-normal distributions, respectively) along with a 95% confidence interval. For dichotomous outcomes, the relative risk and number needed to treat will be determined along with a 95% confidence interval. All comparisons will be made between the randomised exposed (group A) and the unexposed (group B) infants born by CS. Furthermore, all analyses will compare infants from both CS groups together (groups A and B) with children born vaginally (group C) and lastly infants born vaginally will be compared with the two CS groups separately. Differences between study groups will be considered significant if *p* < 0.05.

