### Trial status

Recruitment started in February 2015 following approval from the local ethics committee. Since participants are being recruited from only one tertiary hospital and only women with uncomplicated pregnancies scheduled for a CS are included, the recruitment rate is rather low. Enrolment is expected to be complete by August 2019. Protocol version 3.0 was approved by the regional ethics committee on 29 January 2019.

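### Blinding stops at the statistician, although the primary outcome is produced in the laboratory, where coded tubes would be enough to mask those who process the samples

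*Protocol article*

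**What the plan says.** - Who is blinded (Protocol article, Subjects and study population): "Allocation to a group will be blinded only for the statistician performing the analysis".
- What is judged (Statistical analysis): "The primary outcome will be differences in the microbiota between the two groups of infants born by CS on day 28".
- How it is produced (DNA extraction and microbiota analysis): "DNA will be extracted, as documented previously by" a cited method, then "extracts of the V3-V4 hypervariable regions of the bacterial 16S rRNA gene will be amplified", and "Sequencing will be performed by LifeSequencing SL (Valencia, Spain) on an Illumina MiSeq instrument". The Statistical analysis section adds clustering, chimera removal and rarefaction.
- Coding (Data management and monitoring): "All study participants will receive a study identification number". Nothing says that this number hides the arm from those who handle samples.
- Specimens (legend to Fig. 1): assessments are the same in all groups, "except the umbilical cord blood sample, which will be collected for group A only".
- Timing (Trial status): "Recruitment started in February 2015", with enrolment expected to finish in August 2019.

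**The concern.** The word *only* is a positive statement about who is blinded. It excludes the people who extract DNA, amplify, sequence and process reads, so this is more than a detail that a condensed article left out.

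The treatment itself is given openly, so masking the measurement is the main protection left for a laboratory outcome. Several steps there involve judgement: which samples go together in a batch, which low-yield samples are repeated or dropped, and how deep to rarefy. If any of these choices followed the arm, the result would look like an effect of antibiotic timing. Blinding the statistician comes too late to prevent that.

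The group-A-only cord blood adds a practical route to unblinding: anyone who sees which specimens exist for a study number can identify the group A infants.

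**Working it through.** **1. The text.** Set side by side, the sections listed above give a laboratory outcome, blinding confined to the analyst, identifiers with no stated masking function, and one specimen type unique to one arm. No section masks any laboratory step.

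**2. No figure to reproduce.** The protocol gives no power calculation, SD or batch effect. The numbers below are illustrations under stated assumptions.

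**3. Inputs.** From the document: 20 infants per randomised arm, permuted blocks of 10, significance at p < 0.05. Assumed: a two-sided test, 5 + 5 within each block, two processing batches, a batch shift of 0.5 or 1.0 within-batch SD, no true effect, and a two-sample t-test that ignores batch.

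**4. If samples were sorted by arm.** Bias = batch shift × (share of A in batch 1 − share of B in batch 1). With 14 of 20 A and 6 of 20 B in batch 1:
- 0.5 × (0.70 − 0.30) = 0.2 SD
- 1.0 × (0.70 − 0.30) = 0.4 SD

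Type I error from 40,000 simulated trials per setting:

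| Batch 1, A v B | Difference | Shift 0.5 SD | Shift 1.0 SD |
|---|---|---|---|
| 10 v 10 | 0 | 4.3% | 2.8% |
| 12 v 8 | 4 | 5.4% | 6.3% |
| 14 v 6 | 8 | 8.5% | 18% |
| 20 v 0 | 20 | 34% | 87% |

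For scale, 20 per arm has 80% power for a true difference of about 0.89 SD.

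**5. If batches follow enrolment order.** Every completed block is balanced, so a single cut into two batches can unbalance only the block it falls in, by at most 5 infants. The bias is then at most 0.5 × 5/20 = 0.125 SD or 1.0 × 5/20 = 0.25 SD, and that extreme is rare. In 40,000 simulated trials per cut point (after infant 12, 14, 15, 16, 18, 20, 23 or 25), a difference of 4 or more arose in at most 5% of trials and a difference of 5 in under 1%. The type I error was 4.3-4.8% for a 0.5 SD shift and 2.7-3.6% for 1.0 SD, so below nominal throughout.

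**6. More than two batches.** Batches of 10 or 20 are exactly balanced. For batches of 12, 16 and 24, the largest A-B difference in any batch averaged 2.4, 1.8 and 1.1 infants over 4,000 randomisation lists (maximum 8, 6 and 4). Type I error was not simulated here. The reasoning carries over, because membership of an enrolment-order batch does not depend on the arm.

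**7. What this leaves.** The 14 v 6 and 20 v 0 rows need differences of 8 and 20, which a single enrolment-order cut cannot produce. They describe handling by arm, which is what masking would prevent.

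**The case against.** The strongest reply is that this is a condensed article. Batch layout, rules for repeats and rarefaction depth usually belong in the full protocol, a laboratory procedure or the analysis plan. Their absence here is not an error, and that part of the reply stands. The readout is also instrument-based and sequencing is done by an external company, so that step may well be masked in practice. Nothing says that laboratory staff receive the allocation list or that tubes show the arm.

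A reader might infer more from the 54 months between February 2015 and August 2019: that batches are likely to line up with arm and that the A v B type I error is therefore inflated to 18% or even 87%. The document does not support this. Batches formed over calendar time are what blocked randomisation protects against. Faecal samples are frozen at −20 °C, so processing them all together is equally compatible with the text. The inflated figures require sorting by arm, which no section states.

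A reader might also infer that the contrasts with vaginally born infants are seriously exposed because group C lies outside the blocks. The protocol recruits all three groups at the same time, and those contrasts are non-randomised and not primary, so this adds little.

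The sentence on blinding itself survives the reply. It does not leave laboratory masking open; as worded, it rules it out.

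**Conclusion.** The point holds as a matter of who is blinded. The protocol confines blinding to the statistician, while the primary A v B outcome is generated by unmasked steps in which knowledge of the arm could matter, and group-A-only cord blood can disclose the arm.

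The size of any resulting bias is unknown. The type I error is at or below about 5% if batches follow enrolment order and handling does not depend on arm. It rises materially only if samples are sorted or treated by arm, and then by an amount that depends on an assumed batch shift of 0.5-1.0 SD. The simulations measure batch alignment only; they do not measure the effect of knowing the arm on repeats, exclusions or rarefaction depth, for which the document offers no basis.

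Masking is the firm recommendation. Mixed batches are a separate, optional safeguard: masked staff can still run unbalanced batches, and unmasked staff can run balanced ones.

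**What to change.** Replace the sentence on blinding with:

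*Laboratory, sequencing and read-processing staff and the statistician will work from sample codes that do not reveal the group; repeat, exclusion and rarefaction-depth decisions will be made before the code is broken.*

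The codes on stool samples should not be linkable by those staff to the cord-blood inventory. As an inexpensive safeguard, mix samples from groups A, B and C in random order within extraction and sequencing batches, and record the batch.

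The cost is not zero: a coded list must be kept, and stools may have to be held until a mixed batch can be run. If the laboratory already works from such codes, correcting the sentence is enough. If not, the change has to precede processing, because a batch that coincides completely with arm cannot be separated from the treatment effect afterwards.
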